## **9 STATISTICS**

### **9.1 Sample Size Calculation**

The planned number of subjects is 150 in total, 100 should receive M01ZH09 oral typhoid vaccine and 50 placebo. No formal statistical calculations of sample size were appropriate. The number to include was based upon clinical judgement for both the assessment of safety and determination of immunogenicity. The latter from a consideration of the immunogenicity rates observed in M01ZH09 adult studies completed thus far and the immunogenicity rates observed in children, for typhoid vaccines currently on the market.

### **9.2 Statistical Methods**

#### **9.2.1 General Points**

Analyses will be primarily conducted to estimate parameters of interest such as the proportion of subjects that develop an immune response. Due to the exploratory nature of the study, no adjustment will be made for multiplicity. All available data from withdrawn subjects will be included in the analysis up to the time of withdrawal where possible.

Any deviation(s) from the original statistical analysis plan (SAP) (which will be finalised prior to database lock) will be described and justified in the final report.

#### **9.2.2 Admission Profile**

Demographics and other baseline data will be listed and summarised. Continuous variables (such as age, weight) will be summarised by numbers of subjects, means, medians, standard deviations, minima and maxima. Categorical variables (such as race, sex) will be summarised by counts and percentages in each category.

#### **9.2.3 Study Populations**

The safety population will include all subjects who received a dose of study medication.

The intention-to-treat (ITT) population will include all subjects who received a dose of study medication who have post-baseline immunogenicity data available. The ITT population will be considered the primary population of interest for the immunogenicity endpoints.

The per-protocol (PP) population analysis will be a subset of the ITT population and will be subjects who are not major protocol violators with regards to the inclusion/exclusion criteria, are compliant with study medication and concomitant medications. The SAP will define the exact criteria for exclusion from the PP population.

#### **9.2.4 Safety Endpoints**

##### **9.2.4.1 Primary**

The proportion of subjects reporting SAEs attributed to the study medication

#### 9.2.4.2 Secondary

The proportion of subjects;

- Experiencing symptomatic elevated body temperature, of 38.5 C or greater, in the 14 days following dosing, attributed to study medication.
- Demonstrating persistent (after Day 7) faecal shedding of *S. typhi* (Ty2 *aroC* *ssaV*) ZH9.
- Withdrawn from the study due to adverse events, including bacteraemia attributed to study medication
- With clinically significant changes in laboratory parameters, from Day 0 to any time post dosing, which are attributed to study medication.

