|--|---------------------------------------------------------------------------------------------------------------------------------------------------------------------------------------------------------------------------------------------------------------------------------------------------------------------------------------------------------------------------------------------------------------------------------------------------------------------------------------------------------------------------|
|  | 
interval for each treatment group.
 
In addition, the number and percentage of subjects with defined immune response will be presented by type of assay.
 
For the safety endpoints, the proportion of subjects that have a SAE, attributed to the study medication, will be compared between groups. The proportion of subjects with symptomatic elevation in body temperature, persistent faecal shedding and clinically significant changes in laboratory parameters will be compared between groups.
 |
|--|---------------------------------------------------------------------------------------------------------------------------------------------------------------------------------------------------------------------------------------------------------------------------------------------------------------------------------------------------------------------------------------------------------------------------------------------------------------------------------------------------------------------------|

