##### **3.3.2 Secondary**

The proportion of subjects;

- Experiencing an elevated body temperature, of 38.5°C or greater, in the 14 days following dosing, attributed to study medication.
- Demonstrating persistent (after Day 7) faecal shedding of *S. typhi* (Ty2 *aroC* *ssaV*) ZH9.
- Withdrawn from the study due to adverse events, including bacteraemia, attributed to study medication.
- With clinically significant changes in laboratory parameters, from Day 0 to any time post dosing, which are attributed to study medication.

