### **4.2 Rationale for Study Design**

The study will be conducted following the principles of a double blind study, as per the accepted norm as the gold standard for these types of study. While this is the intent, perfect blinding cannot be guaranteed for a number of reasons (see Section 4.5, Blinding). The placebo serves as a measure of background adverse events and wild-type typhi immunogenicity markers. Allowing more children in the range 5-10 years of age will increase the data available in the age group to likely be employed for Phase III field trials.

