### **4.5 Blinding**

Active vaccine and matching placebo will be packaged identically but with a unique sequential number. This number will enable identification of the contents in case of emergency when used

with the randomisation code break. Preparation of both active and placebo doses will be identical. Hence the investigator and his staff will be essentially blinded in that knowledge of the product supplied to the subjects will remain unknown. However, three areas remain where unintentional unblinding may occur.

1. The placebo and M01ZH09 solutions differ slightly in taste and aroma. Individual subjects will be unaware of any differences in dosing solutions and consequently will be blinded to their treatment in the study. The investigator may detect a difference between the products based on the aroma. A double observer design would reduce this risk but personnel with paediatric expertise at the site are limited, and a double observer design is unlikely to be possible.
2. Subjects will have stool samples taken for culturing and it is anticipated that subjects receiving M01ZH09 will shed *S. typhi* (Ty2 *aroC* *ssaV*) ZH9 in their stools. Results from the stool microbiology will therefore potentially unblind the investigator. It is intended to request that the Investigator does not review these microbiology reports for at least the first 14 days post dosing.
3. Subjects will have blood samples taken for the determination of IgG and IgA specific to *S. typhi*. Subjects that develop an immune response will clearly be identifiable as having received M01ZH09. For this reason it is intended to request that the Investigator does not review these immunology results for at least the first 14 days post dosing.

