### **7.2.4 Diary Card**

Each subject will complete a Diary Card daily for the 14 days following administration of study medication. The subject will record his/her temperature or have their temperature recorded, twice in the morning (15 minutes apart) soon after getting up and twice at bedtime (15 minutes apart), as well as recording all adverse events. Subjects will be instructed that:

- Should their temperature be confirmed as  $\geq 38.5^{\circ}\text{C}$  on both readings, measured 15 minutes apart, or reach  $39.0^{\circ}\text{C}$  or above on any reading, to contact and visit the investigative site as soon as is practical, to have a clinical assessment and initiation of appropriate investigations and therapy.
- Should they feel feverish they should make additional recordings of their temperature and contact the investigative site
- Should they experience any of the following events with moderate or severe intensity they should contact the investigative site and be prepared to make an additional visit:
  - Flushed face
  - Hot, dry skin
  - Low output of urine and/or dark urine
  - Loss of interest in eating
  - Constipation or diarrhoea
  - Vomiting
  - Headache
  - Aching all over
  - Nausea
  - Chills
  - Abdominal pain, cramps or discomfort

- Subjects will also conduct a stool assessment after each bowel movement. The time of passing the stool will be recorded and the stool assessed as 'Normal', 'Soft but in one piece', 'thick liquid', or 'with rice and water'. The observer will also be asked to record if any blood was visible.

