### **8.1.6 Fever Definition**

Fever is defined as an oral temperature of  $\geq 38.5^{\circ}\text{C}$ . Severe fever is defined as an oral temperature of  $\geq 39.5^{\circ}\text{C}$ . All subjects will be asked to take their temperatures twice a day in the morning when they get up and in the evening when they go to bed for the first 14 days post-dosing.

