### 9.3 Methods of Analysis for Safety Variables

All safety summaries will be carried out on the safety population defined in Section 9.2.3.

Summary statistics will be used to present the number of subjects receiving M01ZHZ09 oral typhoid vaccine and placebo.

The numbers of subjects reporting adverse events will be summarised by body system and by MedDRA (version 8.1 or later) preferred term. All adverse experiences recorded after vaccination will be summarised and listed. Adverse events with missing or incomplete onset dates will be assumed to be post-dosing adverse events. Summaries will also be produced showing adverse events by severity, seriousness and relationship to treatment.

The numbers of subjects withdrawn from the study due to adverse events, including bacteraemia attributed to *S. typhi* (Ty2 *aroC* *ssaV*) ZH9, will be presented separately.

Counts will be based on the number of subjects experiencing an event and not the number of events experienced e.g. if a subject reports the same adverse event on three occasions that adverse event will be counted once. Subjects reporting more than one adverse event in a body system will be counted only once in the body system total.

The number and percentage of subjects will be presented, by Visit and overall, that:

- Experience symptomatic elevated body temperature in the 14 days following dosing, attributed to study medication
- Demonstrate persistent (after Day 7) faecal shedding of *S. typhi* (Ty2 *aroC* *ssaV*) ZH9
- Have clinically significant changes in laboratory parameters from Day 0 to any time post dosing which are attributed to study medication.

Laboratory results will be listed with values that are outside the laboratory normal range flagged. For each parameter the overall numbers of values that are within the pre-determined clinically important range at Day 0 but outside the range post-treatment will be summarised.

Vital signs and physical examination results will be summarised by visit.

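### The secondary fever endpoint is worded inconsistently across the protocol, and its endpoint statements count only fevers the investigator attributes to study medication, which leaves the group comparison open to differential attribution

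*Protocol*

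**What the plan says.** The protocol states the fever endpoint in five places.

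- Section 3.3.2: "Experiencing an elevated body temperature, of 38.5°C or greater, in the 14 days following dosing, attributed to study medication". The endpoint list in the summary (section 1) says the same.
- Section 9.2.4.2: "Experiencing symptomatic elevated body temperature, of 38.5 C or greater, in the 14 days following dosing, attributed to study medication".
- Section 9.3, the analysis method: "Experience symptomatic elevated body temperature in the 14 days following dosing, attributed to study medication", to be given as number and percentage by visit and overall.
- The summary's statistical analysis text: "The proportion of subjects with symptomatic elevation in body temperature, persistent faecal shedding" and laboratory changes are to be compared between groups.

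Section 8.1.6 defines fever as an oral temperature of at least 38.5°C, with no mention of symptoms. Section 8.1.4 gives the causality judgement to the investigator, on a scale of probably, possibly or unlikely. On blinding, section 4.5 says "The investigator may detect a difference between the products based on the aroma" and considers a second observer unlikely to be feasible. Section 4.2 explains the control arm: "The placebo serves as a measure of background adverse events and wild-type typhi immunogenicity markers".

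**The concern.** An endpoint with several incompatible definitions is not fixed in advance. A later analysis plan could follow one section only by departing from another, and the choice could be made after temperatures are known.

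The attribution condition is a separate weakness. Temperature is measured, and a randomised placebo arm already separates background fever from vaccine fever. Counting only fevers judged to be caused by study medication puts an opinion between the measurement and the comparison. If that opinion is influenced by a guess at the allocation, a difference between arms can be created or hidden. The primary SAE endpoint and the laboratory endpoint carry the same condition.

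**Working it through.** **Step 1. The wordings side by side**

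| Place | 38.5°C stated | Symptoms required | 14-day window | Attribution required |
|---|---|---|---|---|
| Summary, endpoint list | yes | no | yes | yes |
| 3.3.2 | yes | no | yes | yes |
| 9.2.4.2 | yes | yes | yes | yes |
| 9.3 | no | yes | yes | yes |
| Summary, analysis text | no | yes | no | no |

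Take two children whose fevers are attributed to study medication. One at 38.7°C without symptoms counts under 3.3.2 and not under 9.2.4.2 or 9.3. One at 38.3°C with symptoms could count under 9.3 as written and not under 3.3.2 or 9.2.4.2.

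**Step 2. Does the threshold matter in the sponsor's own data?** Section 2.4 reports pyrexia in MS01.03 over a range of 37.4 to 38.7°C. Leaving out the one case judged unrelated, 3 of the 16 subjects at 5 × 10^9 CFU had pyrexia. One subject in that dose group is reported at 38.3°C and another at up to 38.7°C. I take both to be among the 3; the third temperature is not given.

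- No threshold: 3/16 = 18.8% (exact 95% CI 4.1 to 45.7%).
- 38.5°C threshold: 1/16 = 6.3% or 2/16 = 12.5%, depending on the third subject.

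The effect of *symptomatic* cannot be computed from the documents.

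**Step 3. What could attribution do?** The protocol gives no assumed fever rate, attribution rate or test for fever, so every rate below is an assumption. Let the true fever rate f be the same in both arms, and let q be the share of fevers attributed in an arm. The apparent rate is f × q. The arms are 100 and 50 (section 9.1). The 95% half-width is 1.96 × √(p1(1−p1)/100 + p2(1−p2)/50). The last column is the exact rejection rate of a two-sided Fisher test at 0.05.

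| f | q vaccine / placebo | Apparent rates | Ratio | Half-width | Rejection |
|---|---|---|---|---|---|
| 10% | 60% / 60% | 6% v 6% | 1.0 | 8.1 points | 2.9% |
| 10% | 70% / 50% | 7% v 5% | 1.4 | 7.8 points | 3.1% |
| 10% | 80% / 40% | 8% v 4% | 2.0 | 7.6 points | 7.1% |
| 10% | 90% / 20% | 9% v 2% | 4.5 | 6.8 points | 24.6% |
| 5% | 80% / 40% | 4% v 2% | 2.0 | 5.5 points | 1.0% |
| 20% | 80% / 40% | 16% v 8% | 2.0 | 10.4 points | 23.4% |

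Guessing the allocation is one way to get unequal q. Suppose 50% of fevers are attributed when the investigator believes the child had vaccine and 10% when placebo is believed, with f = 10%.

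- 70% correct guesses: vaccine 0.10 × (0.7 × 0.5 + 0.3 × 0.1) = 3.8%; placebo 0.10 × (0.3 × 0.5 + 0.7 × 0.1) = 2.2%; ratio 1.7.
- 90% correct guesses: 0.10 × (0.9 × 0.5 + 0.1 × 0.1) = 4.6%; 0.10 × (0.1 × 0.5 + 0.9 × 0.1) = 1.4%; ratio 3.3.

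In every row the expected difference in all-cause fever is zero.

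**Step 4. Reading schedule.** Section 8.1.6 asks for two readings a day. Section 7.2.4 asks for two readings 15 minutes apart on each of the same two occasions, so four a day. Section 7.2.4 also uses confirmation on both readings to trigger contact with the site, while no endpoint statement says whether a single reading counts.

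**The case against.** Much can be said for the plan.

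- The threshold missing from 9.3 may be shorthand, since 9.2.4.2 and 8.1.6 both give 38.5°C. That is plausible. It leaves the conflict over *symptomatic* untouched.
- Section 9.3 also summarises all post-vaccination adverse events by preferred term whatever their relationship, laboratory values that leave the clinically important range without an attribution condition, and vital signs by visit. Much all-cause information will therefore exist. None of these tables fixes a 38.5°C cut-off, and none is the named endpoint.
- Packaging and preparation are identical. The investigator is to be asked not to review stool or immunology results for at least 14 days, which covers the fever window, and ELISA sera are shipped only after all subjects have reached the relevant day. This stands. It is only a request, though, and it does nothing about aroma.
- No subject in MS01.07, the adult Vietnamese study, had fever. If background fever in children is also low, the absolute distortion is small.

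Four stronger readings are tempting and not supported. A reader might infer that the fever comparison is biased; the documents show only an opening for bias, and the sizes above rest on assumed inputs. A reader might take the filter to apply to vaccine alone; the text says study medication, so it applies in both arms. A reader might think the two-versus-four reading discrepancy biases the comparison; it affects both arms alike and can alter only how many fevers are detected. A reader might think the children's protection depends on the attributed endpoint; the fever rules for suspending dosing in Table 1 carry no attribution or symptom condition.

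**Conclusion.** The inconsistency is certain from the text: the symptom requirement is present in some statements and absent in others, the threshold is missing from two of them, and *symptomatic* is undefined. On the sponsor's own adult data, the threshold alone moves a count from 3 of 16 to 1 or 2 of 16, given how the three cases were identified.

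The attribution problem is a risk. Over the assumed shares in the table, equal true rates give an apparent ratio of up to 4.5. In the middle case at a 10% rate, that means about 8 of 100 children against 2 of 50, with a rejection rate of 7.1%. It would be wrong to say that every statement carries the filter, because the summary's analysis text does not; that is one more inconsistency.

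This is a secondary endpoint in a study the protocol calls exploratory, with no formal sample size. Severity is moderate: it should be fixed.

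**What to change.** - Use one wording in both places in the summary and in 3.3.2, 9.2.4.2 and 9.3: the proportion of subjects with an oral temperature of 38.5°C or more (the threshold in 8.1.6) from dosing to Day 14, regardless of symptoms or attribution.
- State whether a single reading or a confirmed pair counts.
- Report it by arm with the difference and 95% CI.
- Keep attributed and symptomatic fever as supportive tables. Define *symptomatic*, and say which causality grades in 8.1.4 count as attributed.
- Present all-cause SAEs and all-cause clinically significant laboratory changes by arm beside the attributed endpoints. The primary safety endpoint itself need not be replaced.
- Reconcile the diary reading schedule in 7.2.4 with 8.1.6.

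The cost is an amendment to wording and a few extra tables, because the temperatures and events are already recorded. The downside is that fever percentages will be higher in both arms than under the attributed definition, and the report should say why.

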#### 9.2.5 Immunogenicity Endpoints

Assessment of the immune response will be made by determining the proportion of subjects who;

- Develop a positive immune response\* to *S. typhi* LPS as assessed by an increase in *S. typhi* LPS specific IgG at either Day 14 or Day 28.
- Develop a positive immune response\* to *S. typhi* LPS as assessed by an increase in *S. typhi* LPS specific IgA at either Day 7 or Day 14.
- At Day 7, have = 4 ASCs per 10^6 PBMC, secreting IgA specific for *S. typhi* LPS detected by ELISPOT assay\*\*.

\*The definition of a 'positive immune response' will be determined following the completion of assay development.

\*\*An ELISPOT Day 0 result of = 4 ASCs per 10^6 PBMC constitutes a pre-vaccination positive and the subject will be excluded from the analysis of the ELISPOT results.

### 9.3 Methods of Analysis for Safety Variables

All safety summaries will be carried out on the safety population defined in Section 9.2.3.

Summary statistics will be used to present the number of subjects receiving M01ZHZ09 oral typhoid vaccine and placebo.

The numbers of subjects reporting adverse events will be summarised by body system and by MedDRA (version 8.1 or later) preferred term. All adverse experiences recorded after vaccination will be summarised and listed. Adverse events with missing or incomplete onset dates will be assumed to be post-dosing adverse events. Summaries will also be produced showing adverse events by severity, seriousness and relationship to treatment.

The numbers of subjects withdrawn from the study due to adverse events, including bacteraemia attributed to *S. typhi* (Ty2 *aroC* *ssaV*) ZH9, will be presented separately.

Counts will be based on the number of subjects experiencing an event and not the number of events experienced e.g. if a subject reports the same adverse event on three occasions that adverse event will be counted once. Subjects reporting more than one adverse event in a body system will be counted only once in the body system total.

The number and percentage of subjects will be presented, by Visit and overall, that:

- Experience symptomatic elevated body temperature in the 14 days following dosing, attributed to study medication
- Demonstrate persistent (after Day 7) faecal shedding of *S. typhi* (Ty2 *aroC* *ssaV*) ZH9
- Have clinically significant changes in laboratory parameters from Day 0 to any time post dosing which are attributed to study medication.

Laboratory results will be listed with values that are outside the laboratory normal range flagged. For each parameter the overall numbers of values that are within the pre-determined clinically important range at Day 0 but outside the range post-treatment will be summarised.

Vital signs and physical examination results will be summarised by visit.

#### **9.4 Methods of Analysis for Immunogenicity Endpoint**

The primary outcome measure in this study will be the proportion of subjects with a positive immune response (a positive serum IgG and/or a positive serum IgA response and/or an increase in the number of ELISPOTS). The proportion of subjects who satisfy the immunogenicity endpoint will be compared between the vaccine and placebo groups. The treatment difference and associated 95% confidence interval will be presented.

The number and percentage of subjects with an immune response will be presented along with the two-sided 95% confidence interval for each treatment group.

In addition, the number and percentage of subjects with defined immune response will be presented by type of assay.

